### Allocation concealment mechanism

Following central computer randomisation, participants’ assignments to either immediate or deferred COVID-19 booster will appear on the screen. The randomisation screen will be printed and form part of participants’ study records. The screen print plus a prescription will be provided to an on-site clinical trials pharmacy for dispensing of the DT vaccine.

### Implementation

Members of the site’s research team will enrol participants who will be randomly assigned to the intervention as described. The DT booster will be administered at the site by a qualified member of the research team. The COVID-19 booster will be administered at local vaccination sites.

### Blinding

This study was implemented in Sydney, Australia during the pandemic phase of COVID-19. During that time, the New South Wales (NSW) Ministry of Health had control over the limited supply of COVID-19 vaccine. Hence, we were unable to secure a supply of vaccines for the study. Therefore, the trial was designed so that COVID-19 boosters could be given within the state government mandated vaccination hubs and centres. As there were no supply or administration restrictions for the DT booster, it could be given to participants at the hospital study sites by research staff. Therefore, due to the different administration locations for the COVID-19 and DT vaccines, it was not possible to blind either the participants or research staff.

### Data collection methods

Following enrolment, research coordinators will collect relevant demographics (age, gender, ethnicity) and clinical data (vital signs, physical measurements, study-qualifying disease diagnosis and treatment plan, medical history, pregnancy status, concomitant medication and COVID-19 infections and vaccinations) on a trial-specific eCRF. Following randomisation and initial booster vaccination, the visit schedule will include eight visits for participants in Group 1 and seven for those in Group 2.

The schedule of study assessments is outlined in online supplemental table 1. Blood samples will be collected at baseline and all on-site follow-up visits for assessment of immunological outcomes. At all study visits, a research coordinator will collect relevant clinical data on the visit eCRF and will review concomitant medication, AEs and SAEs that may have occurred since the last visit. Quality of life assessments at baseline and at weeks 24 and 48 will be self-reported using the validated EQ-5D-3L tool^28^ and participant responses will be entered into the eCRF by the coordinator.

### Plans to promote participant retention and complete follow-up

Each participant will be provided with a visit schedule outlining visit dates and the visit windows so attendance can be planned. Research coordinators will contact participants prior to visits to promote attendance. Regular newsletters will be sent to research sites to promote the study, encourage enrolment and provide updates on progress and retention. Refresher training video meetings will also be conducted if necessary. Completion of study data will be checked at regular intervals by the main study coordinator.

### Data management

Research data collected on eCRFs and study-specific forms will be stored in a secure password-protected, encrypted study-specific clinical trial management system (Research Electronic Data Capture (REDCap) hosted by the sponsor, UNSW Sydney. This electronic data capture (EDC) system contains all clinical data, AEs and questionnaire responses and is based on source documentation maintained at research sites. Trained research coordinators at sites will enter data into the EDC. Automated checks will ensure entered data conform to trial-specific procedures. Data cleaning and quality checks will be conducted on an ongoing basis by trained personnel to ensure data are accurate and complete. Additionally, on-site monitoring visits will be conducted during the trial to verify source documentation is accurate, complete, consistent and adheres to the study protocol. Data will be backed up regularly and only available to study researchers. Data will be stored for a minimum of 15 years following which the storage media will be physically destroyed.

### Statistical methods

#### Statistical methods for analysing primary and secondary outcomes

Baseline participant characteristics will be summarised by randomised arm for each sub-stratum separately and combined. Primary analyses will compare immunogenicity endpoints between randomised arms on an intention-to-treat basis, that is comparing participants as randomised regardless of whether they received immediate or deferred vaccinations according to the protocol. Log_10_ NAb titres will be summarised at each time point and presented graphically within each stratum. The primary outcome will be time-weighted AUC change from baseline in anti-SARS-CoV-2 log_10_ NAb titre over 12 months. The primary analysis will follow a modified intention to treat approach (mITT) and include all randomised participants with a baseline visit and at least one post baseline time point measured. This approach allows for the inclusion of all participants, even with partial follow-up. The AUC will be calculated for each participant using the trapezoidal rule based on all available data. To assess for bias due to missing data, a secondary analysis which will only include patients who completed the study and have no missing data will be performed. These results will be compared with the mITT analysis. Additionally, if the proportion of patients with missing data is over-represented in one study arm, additional sensitivity analyses will be performed. Randomised arms will be compared within each treatment stratum separately using simple, unadjusted two-sample t-tests. In the event of unbalanced baseline characteristics, adjusted comparisons using linear regression methods may be performed. Results will be presented as mean differences, 95% CIs and p values. There will be no adjustment of p values and CIs for multiple comparisons across the seven sub-strata. In addition to analyses within strata, analyses combining all strata will be performed. Analyses will test for different effects of immediate versus deferred vaccination in separate strata by testing for interactions between strata and randomised arm. These results will be presented as forest plots, by strata and overall. Analysis for Group 2 participants will be presented independently using similar approaches as above as appropriate.

Secondary endpoints will include time-weighted AUC change from baseline in anti-tetanus log_10_ NAb titre over 12 months. Analysis will be conducted as described above for the primary endpoint following a mITT approach including all randomised participants with a baseline visit and at least one post baseline time point measured.

A comprehensive statistical analysis plan will be drafted by the study statistician and approved by the PSC prior to data lock. Copies of the analysis plan will be available on request following its finalisation.

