### Outcomes

The primary outcome will be the integrated time-weighted area under the curve (AUC) anti-SARS-CoV-2 NAb response over 12 months from a SARS-CoV-2 booster as assessed by a high-throughput SARS-CoV-2 NAb platform assay developed by our group.^22^,^24^ The assay involves culturing a cell-line that is hyper-permissible to SARS-CoV-2 through the expression of ACE2 and transmembrane serine protease 2 receptors. Serial dilutions of patient serum are then introduced to the cell culture wells in addition to homogenous concentrations of SARS-CoV-2 virions including variants of concern. Anti-spike IgG present in the patient serum acts to block viral entry into the cell. The assay readout is the infectious dose 50% (ID_50_), the viral concentration required to obtain 50% cellular death.

Secondary outcomes include laboratory, safety and clinical/biological outcomes:

Laboratory outcomes:

NAb response to a tetanus toxoid booster integrated over 12 months.Responses to the COVID-19 vaccine includingBreadth of NAb against SARS-CoV-2 variants of concern.Kinetics of NAb over time including responses to variants of concern.Memory T cell, B cell and natural killer (NK) cell responses to peptide sets representing different domains of the SARS-CoV-2 spike protein.Immunological responses as assessed above in populations stratified by broad study-qualifying disease type and different modes of immunosuppression employed such as chemotherapy, BMT, B-cell depleting therapies and cytokine inhibition.

Safety outcomes:

Local and systemic AEs that occur in the 7 days following the DT and COVID-19 vaccinations.AEs following immunisation and adverse drug reactions following immunisation for the duration of the study.COVID-19 vaccine-induced disease flares.On-study PCR-confirmed or rapid antigen-confirmed SARS-CoV-2 infections.All on-study pregnancies.

Clinical/biological outcomes:

Health quality of life scores (EQ-5D-3L) at weeks 0, 24 and 48.Impact of immunosuppression on vaccine protection over time will be assessed by modelling:Level of protection over time based on NAb levels.Boosting and decay of anti-spike IgG, specific memory B, T and NK cell responses.Inform policies on the timing of additional COVID-19 boosters in vulnerable populations about to commence immunosuppression or following BMT.

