### Sample size

The maximum sample size is 320 participants, 280 in the systemic autoimmunity and haemato-oncology group and 40 in the BMT recipient group. This sample size is based on previously calculated integrated time-weighted AUC of live anti-SARS-CoV-2 NAb titres following two SARS-CoV-2 vaccinations in healthy adults^25^ and patients infected with COVID-19.^26 27^ SD calculated from these datasets were 0.11 log_10_ and 0.12 log_10_, respectively. Assuming an SD of 0.12 log_10_, the study will have over 90% power to detect a 0.13 log_10_ difference in time weighted AUC log_10_ change from baseline (2-alpha=5%) within each sub-stratum of 40 participants. This corresponds to a 35% difference in live virus neutralisation titre between randomised arms. Time-weighted AUC allows for varying of follow-up of participants due to missed visits, loss to follow-up or death. We conservatively estimate overall lost to follow-up to be 10% and mortality 1% balanced across randomised sub-strata.

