#### Methods to handle protocol non-adherence and methods to handle missing data

As indicated above, all participants with a minimum of two study visits will be included in the primary analysis, therefore including participants even with incomplete data at every time point, a strength of using an AUC endpoint. There will be no imputations for missing data in the primary outcome. Secondary analyses will also be conducted in a per-protocol (PP) population including only participants with available data at all time-points and received the scheduled interventions. Protocol non-adherers will also be excluded in the PP analyses.

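### With no imputation, the trapezoidal AUC bridges the week-24 booster when no sample was taken just before it, which generally overstates antibody in the deferred arms

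*Protocol article*

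**What the plan says.** Four parts of the protocol article matter here.

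- **Derivation.** Under Statistical methods for analysing primary and secondary outcomes: "The primary outcome will be time-weighted AUC change from baseline in anti-SARS-CoV-2 log_10_ NAb titre over 12 months", and "The AUC will be calculated for each participant using the trapezoidal rule based on all available data". The modified intention-to-treat set is to "include all randomised participants with a baseline visit and at least one post baseline time point measured".
- **Missing data.** Under Methods to handle protocol non-adherence and methods to handle missing data: "There will be no imputations for missing data in the primary outcome", and "all participants with a minimum of two study visits will be included in the primary analysis". Tolerance of gaps is presented as an advantage of the endpoint. Sample size says the same: "Time-weighted AUC allows for varying of follow-up of participants due to missed visits, loss to follow-up or death".
- **Timing.** Sequence generation places the COVID-19 booster at week 0 in Arms A and C and at week 24 in Arms B and D. Participant timeline gives 12 months of visits. Implementation adds that "The COVID-19 booster will be administered at local vaccination sites", so a missed study sample does not mean a missed booster.
- **Window.** The Outcomes section words the window differently: "NAb response over 12 months from a SARS-CoV-2 booster".

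No exception is stated for an interval that contains a vaccination.

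**The concern.** A trapezoid bridges a missed visit acceptably when log titre is roughly linear across the gap. In the deferred arms a jump is planned at week 24. If the sample just before it is missing, or if the off-site booster is taken before the week-24 blood draw, the rule draws a straight ramp from the last earlier sample to the first post-booster sample. Part of the booster response is then counted in weeks when the participant had not been boosted.

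The two arms are not exposed equally. In the immediate arms the pre-booster sample is the baseline, which the analysis set requires. In the deferred arms the equivalent sample is optional. The result is generally a shift of the primary contrast towards deferral. A larger sample does not shrink such a shift, so relative to the standard error it weighs most in the pooled Group 1 analysis. The anti-tetanus AUC is to be analysed in the same way, so Arm A, which receives its DT booster at week 24, has the mirror-image problem.

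**Working it through.** **The plan's own figure.** Inputs from Sample size: SD 0.12 log10, difference 0.13 log10, two-sided 5%, 40 per sub-stratum, hence 20 per arm at 1:1. The standard error is 0.12 × √(2/20) = 0.0379, and 0.13/0.0379 = 3.43. Power is 92.9% by the normal approximation and 91.6% by the noncentral t. The stated power of over 90% reproduces.

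**Excess for one affected participant.** Take the window as weeks 0–48, a flat titre before the booster, a last earlier sample at week p, a first post-booster sample at week q, and rise R at week q.

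- Area from p to q with the week-24 sample: ½(q − 24)R.
- Area from p to q without it: ½(q − p)R.
- Difference divided by 48 weeks: R(24 − p)/96. It does not depend on q.

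Example with p = 12, q = 28, R = 1.0: the areas are 2.0 and 8.0 log10-weeks, and the excess is 6.0/48 = 0.125 log10.

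The sampling weeks are in a supplement that is not shown, so p is an assumption:

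| Last earlier sample | Excess | R = 0.3 | R = 0.5 | R = 1.0 |
|---|---|---|---|---|
| Week 20 | 0.042 × R | 0.013 | 0.021 | 0.042 |
| Week 18 | 0.0625 × R | 0.019 | 0.031 | 0.0625 |
| Week 12 | 0.125 × R | 0.0375 | 0.0625 | 0.125 |

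At week 12 these are 29%, 48% and 96% of the 0.13 design difference. If the titre wanes by w between weeks 12 and 24, with R measured from the week-24 value and q = 28, the excess becomes (6R + 2w)/48. Waning therefore adds to it.

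**The same missed visit in the immediate arm.** If log10 titre falls linearly through week 24, the chord lies on the true line and the error is 0. With curved decay it is not exactly 0.

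**Effect on the comparison.** Arm-level bias = fraction affected × excess. The fraction is an assumption, since the protocol gives no rate of missed week-24 samples. The table uses week 12 as the last earlier sample. Power is for a true 0.13 advantage of immediate boosting with 20 per arm. Type I error is for the pooled Group 1 test with 140 per arm, where the standard error is 0.12 × √(2/140) = 0.0143.

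| R | Affected | Bias | Sub-stratum power | Pooled type I error |
|---|---|---|---|---|
| 0.5 | 5% | 0.003 | 90.3% | 5.5% |
| 0.5 | 10% | 0.006 | 88.8% | 7% |
| 1.0 | 5% | 0.006 | 88.8% | 7% |
| 1.0 | 10% | 0.0125 | 85.5% | 14% |

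With a last earlier sample at week 20, R = 0.5 and 10% affected, the bias is 0.002, power 90.7% and pooled type I error 5.2%.

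**The case against.** The strongest reply has five parts.

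- **It belongs in the SAP.** The article promises a full plan before data lock, and handling of dates is derivation detail. This stands only in part. The article does not leave the matter open: it fixes the trapezoid on all available data and rules out imputation. A plan that follows those sentences inherits the error, and one that carries a value to the booster date departs from them.
- **Safeguards exist.** The completer and per-protocol analyses cannot contain the artefact, and a comparison with the primary result might expose it. That is true, but both are secondary and avoid the problem by dropping participants. The further sensitivity analyses are triggered only when missing data are over-represented in one arm, whereas this bias arises with equal missingness.
- **The size is unknown and may be small.** This stands. The sampling weeks, the rise and the miss rate are all assumed. The 10% loss to follow-up in Sample size is not the affected share, because someone lost before week 24 has no later sample to bridge to.
- **The direction is not guaranteed.** This stands. A reader might infer that the error always raises the deferred-arm AUC. An infection between the last sample and week 24 can put the true titre above the chord, and a booster non-responder has an error near zero. Nor is the immediate-arm error exactly zero unless log titre decays linearly.
- **The window may start at the booster.** The Outcomes wording allows that reading, under which pre-booster weeks drop out and the error disappears. However, 12 months from a week-24 booster does not fit into 12 months of follow-up, and the statistical section and Participant timeline imply week 0.

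A reader might also infer that Arm B will miss week 24 more often, because Arm A attends the hospital for DT then. The protocol does not support that. Quality of life is collected at week 24 in everyone, bloods are taken at all on-site follow-up visits, and coordinators contact participants before visits. The point does not need unequal attendance.

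**Conclusion.** The point holds for an AUC window that starts at week 0. As written, the primary derivation gives a wrong value for any boosted deferred-arm participant without a sample just before the booster. The value is generally too high, by about 0.04 × rise (last earlier sample at week 20) to 0.125 × rise (week 12) for a flat pre-booster titre. Balanced missingness does not remove the bias.

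Under moderate assumptions the effect on the trial is modest: the 5–10%, 0.5 log10, week-12 case takes power from 91.6% to 90.3–88.8% and pooled type I error to 5.5–7%. The 14% figure should not be read as the expected inflation. Within the 5–10% range, with a last earlier sample no earlier than week 12, it needs both a 1.0 log10 rise and 10% affected. The change is worth making because the error is systematic, sits in the primary analysis and is cheap to remove.

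**What to change.** In the primary derivation:

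1. Classify each sample as pre- or post-vaccination by the actual vaccination date, not by visit label.
2. Split the AUC at that date and use only pre-vaccination samples before it.
3. Where no sample was taken just before vaccination, carry the last pre-vaccination log10 titre to that date and start the post-vaccination trapezoid from it.
4. Amend the no-imputation sentence under Methods to handle protocol non-adherence and methods to handle missing data to allow this one step.
5. Apply the same rule to the anti-tetanus AUC, where it matters for Arm A, and to Group 2.
6. Reconcile the window in Outcomes with the one in the statistical section.

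The cost is a few lines of text and programming. COVID-19 vaccinations are already collected on the eCRF, and DT is given on site. The small downside is that the carried-forward value ignores modest waning, or an unobserved infection, between the last sample and the booster.

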### Randomisation

#### Sequence generation

Participants will be assigned to a study group based on their study-qualifying medical condition (table 1) using a central computer-generated randomisation sequence with a blocking factor of four created by the study statistician.

Participants in Group 1 will be stratified into one of two supra-stratum, haematological malignancy or systemic autoimmunity and then to sub-strata based on their planned treatment. Sub-strata include: haematological malignancy—chemotherapy; autoimmunity—B-cell depletion therapies; autoimmunity—anti-metabolite therapies; autoimmunity—TNFα-inhibition; autoimmunity—cyclophosphamide or alemtuzumab; autoimmunity—JAKi; autoimmunity—anti IL-17/23 monoclonal antibodies (table 1).

Group 1 participants will be randomised in a 1:1 ratio to receive either a COVID-19 booster at week 0 and a DT booster at week 24 (Arm A: immediate booster), or a DT booster at week 0 and a COVID-19 booster at week 24 (Arm B: deferred booster) (figure 1). Randomisation will be conducted using a central computer-generated random allocation algorithm using blocks and stratified by sub-strata population.

Group 2 has no sub-strata and participants will be randomised in a 1:1 ratio to receive either an immediate COVID-19 booster at week 0 (Arm C), or a deferred COVID-19 booster at week 24 (Arm D) (figure 1).

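### The primary t-test on change from baseline is valid, but prespecified adjustment for the week-0 titre would be at least as precise in most cases and would replace an adjustment rule triggered by observed imbalance

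*Protocol article*

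**What the plan says.** In the protocol article, the section on statistical methods for primary and secondary outcomes defines the endpoint: "The primary outcome will be time-weighted AUC change from baseline in anti-SARS-CoV-2 log_10_ NAb titre over 12 months". It then names the test: "Randomised arms will be compared within each treatment stratum separately using simple, unadjusted two-sample t-tests". The next sentence adds: "In the event of unbalanced baseline characteristics, adjusted comparisons using linear regression methods may be performed". The article gives no criterion for imbalance and no covariates, and it does not say whether an adjusted result would support the t-test or take precedence over it.

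The baseline titre will be available. Under data collection methods: "Blood samples will be collected at baseline and all on-site follow-up visits for assessment of immunological outcomes". The primary analysis set is to "include all randomised participants with a baseline visit and at least one post baseline time point measured".

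On allocation, the sequence generation section states: "Randomisation will be conducted using a central computer-generated random allocation algorithm using blocks and stratified by sub-strata population". On power, the sample size section states: "Assuming an SD of 0.12 log_10_, the study will have over 90% power to detect a 0.13 log_10_ difference" in time-weighted AUC change, two-sided at 5%, in each sub-stratum of 40. With 1:1 allocation that is 20 per arm.

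**The concern.** Subtracting the baseline is not the same as adjusting for it. A change score assumes that each unit of baseline log10 titre carries over as exactly one unit at follow-up. If the true slope is below 1, as it would be if people with low titres have more room to rise, the change score remains correlated with baseline. Two things follow. Its variance is larger than that of an analysis that estimates the slope. And a chance difference in baseline between arms leaks into the estimated effect in that particular sample. With 20 per arm, such differences are not rare.

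The plan's response is to consider adjustment after imbalance has been seen. That leaves an avoidable choice open in an open-label trial. It concerns a covariate whose relevance is known in advance and which is to be measured in everyone analysed.

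**Working it through.** **Inputs.** From the sample size section: SD 0.12 log10, difference 0.13 log10, two-sided 5%, 40 per sub-stratum. From the sequence generation section: 1:1 allocation, so n = 20 per arm. Not in the article, and therefore assumed: the correlation r between baseline log10 titre and the time-weighted follow-up mean (0.3 to 0.9), with equal variances at the two times.

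**The plan's own figure.** The standardised difference is 0.13 / (0.12 × √(2/20)) = 0.13 / 0.0379 = 3.43. Power is Φ(3.43 − 1.96) = 0.929 by the normal approximation and 0.916 by noncentral t on 38 df. Both exceed 90%, so the stated power reproduces for the planned test.

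**Baseline-adjusted model.** With equal variances σ² at both times:
- Var(change) = 2σ²(1 − r)
- residual variance after adjustment = σ²(1 − r²)
- ratio = (1 + r)/2
- adjusted SD = 0.12 × √((1 + r)/2)

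Power uses noncentral t on 37 df with the SD inflated by √(1 + 1/37) for estimating the slope. Holding SD(change) at 0.12 also fixes the baseline SD implied by each r: σ = 0.12 / √(2(1 − r)).

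| r | variance ratio | adjusted SD | power, 20 per arm | implied baseline SD |
|---|---|---|---|---|
| unadjusted change | 1 | 0.120 | 0.916 | – |
| 0.3 | 0.65 | 0.097 | 0.983 | 0.10 |
| 0.5 | 0.75 | 0.104 | 0.967 | 0.12 |
| 0.7 | 0.85 | 0.111 | 0.946 | 0.155 |
| 0.9 | 0.95 | 0.117 | 0.922 | 0.27 |

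**Limit on the gain.** If baselines vary widely, r must be high for the change to have an SD of only 0.12. For an assumed baseline SD of 0.3, 2(1 − r) = (0.12/0.3)² = 0.16, so r = 0.92 and the ratio is 0.96. For an assumed SD of 0.5, r = 0.97 and the ratio is about 0.99.

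**Equal variances relaxed.** Let k be the follow-up SD divided by the baseline SD. The ratio becomes k²(1 − r²)/(k² + 1 − 2rk). For k from 0.8 to 1.5 and r from 0.3 to 0.9, it runs from 0.50 to 0.998.

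**Exposure to chance imbalance.** The baseline difference between arms has SD σ√(2/20) = 0.316σ. Under equal variances the true slope is r, so (1 − r) of it carries into the change score: 0.022, 0.019, 0.015 or 0.008 log10 (1 SD) for r = 0.3, 0.5, 0.7 or 0.9, against a target of 0.13. In simulation under no effect (20 per arm, 100,000 replicates per setting), among samples where baseline differed at p < 0.05 the change-score t-test rejected in 22%, 18%, 13% and 8% for the same four values of r. Across seven independent sub-strata, the chance that at least one shows such an imbalance is 1 − 0.95⁷ = 30%.

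**Overall type I error, same simulations.**
- Always the t-test, or always the adjusted model: about 5.0%.
- Strict switch to the adjusted model when baseline p < 0.05: 4.1% to 5.0%.
- Smaller p-value taken only once imbalance is declared (trigger p < 0.05 or p < 0.2): 5.1% to 5.5%.
- Smaller p-value taken freely in every sample: 6.1% to 7.8%.

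**The case against.** Much of the case for leaving the plan alone stands.

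A reader might infer that the data choose the primary model. The article does not say so. The t-test is what will be done. Adjusted comparisons are only permitted, and nothing states that they would replace it. A material rise in type I error needs a free choice between results in every comparison, which the text does not offer.

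A reader might also infer that the baseline titre is ignored. It is not: the endpoint subtracts it. Only the difference between a slope fixed at 1 and an estimated slope is lost. Nor is chance imbalance a bias in the test. It is part of the sampling variation that the standard error already reflects, and unconditional type I error is about 5%. The exposure is conditional on the sample in hand.

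The strongest objection concerns size. A 15% to 35% variance reduction requires r between 0.3 and 0.7. With the planning SD of 0.12 and equal variances, that implies baseline SDs of only 0.10 to 0.155 log10. One cannot claim both that baselines vary widely and that the gain is large.

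Finally, the within-stratum comparisons already respect the stratification, and a stratum-by-arm interaction test is planned. The exact pooled model and the covariate list can reasonably sit in the analysis plan.

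What survives is that the article names the less efficient analysis as primary and ties adjustment to observed imbalance, when a prespecified baseline covariate would avoid both at almost no cost.

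**Conclusion.** The point holds as a matter of efficiency and prespecification. The planned test is not invalid, and its stated power is correct. What it gives up is some precision, plus protection against chance baseline imbalance in small sub-strata, whenever the true slope on baseline is not 1.

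Under equal variances and a change-score SD of 0.12, the variance reduction is 35%, 25%, 15% or 5% for r = 0.3, 0.5, 0.7 or 0.9. At the top of that range power moves only from 0.916 to 0.922. Since the article does not give r, no single figure can be claimed. The documents support neither an inflated type I error nor a known large loss of power. The change is still worth making, because it needs no new data and removes a discretionary step.

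**What to change.** - Prespecify as primary, within each sub-stratum and within Group 2, a linear model of the AUC outcome on arm and baseline log10 neutralising titre. For the pooled Group 1 analysis, add sub-stratum.
- Define the covariate as the week-0 sample taken before any randomised vaccination. The outcomes section counts 12 months from the booster, which leaves the time origin unclear for the deferred arms. A week-24 pre-booster value there would be post-randomisation and must not serve as the covariate.
- Delete the sentence that makes adjustment depend on observed imbalance.
- Report the unadjusted t-test as a sensitivity analysis.
- Adjustment for transplant type in Group 2 is optional.

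The endpoint need not change: with the week-0 titre as covariate, the AUC and the AUC minus baseline give the same treatment effect. The cost is a short edit to the protocol and the analysis plan and about one degree of freedom per comparison (37 rather than 38 in a sub-stratum of 40). No extra participants or samples are needed.

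### The primary comparison is an unadjusted t-test on change from baseline, with optional adjustment if arms look unbalanced; an always-fitted ANCOVA on the week 0 titre would be a nearly free improvement

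*Protocol article*

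**What the plan says.** All of this is in the Protocol article. Under the statistical methods for primary and secondary outcomes, the endpoint is defined as a change: "The primary outcome will be time-weighted AUC change from baseline in anti-SARS-CoV-2 log_10_ NAb titre over 12 months". The test is named: "Randomised arms will be compared within each treatment stratum separately using simple, unadjusted two-sample t-tests". Adjustment is conditional and optional: "In the event of unbalanced baseline characteristics, adjusted comparisons using linear regression methods may be performed". The text does not name the covariates.

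The same section carries similar methods to Group 2, and for the anti-tetanus endpoint says "Analysis will be conducted as described above for the primary endpoint". It also plans an analysis combining all strata, with no baseline covariate mentioned.

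The baseline titre is already collected. The modified intention-to-treat set will "include all randomised participants with a baseline visit and at least one post baseline time point measured", and the data collection section says "Blood samples will be collected at baseline and all on-site follow-up visits for assessment of immunological outcomes". A change from baseline could not be computed without it.

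The sample size section powers each sub-stratum of 40 on the same change score: "Assuming an SD of 0.12 log_10_, the study will have over 90% power" for a difference of 0.13 log10 at two-sided 5%.

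**The concern.** Analysing a change score is the same as regressing follow-up on baseline with the slope forced to 1. If the true slope is below 1, subtracting baseline over-corrects any chance difference in baseline titre between two arms of 20, and the confidence interval is wider than the data allow. ANCOVA estimates the slope instead.

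The conditional clause does not solve this. Whether an adjusted result appears depends on how the arms happen to look, and that judgement can be made separately in each of seven sub-strata. Adjustment for a prognostic baseline value is most useful when it is fixed in advance and always applied.

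At stake is precision within small strata. The power there depends on an SD taken from healthy vaccinees and patients infected with COVID-19, not from the immunosuppressed population being enrolled.

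**Working it through.** **Inputs from the sample size and randomisation sections.** Sub-stratum N = 40, 1:1, so 20 per arm; SD of the change 0.12 log10; difference 0.13 log10; two-sided alpha 5%.

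**Step 1: reproduce the plan's figure.** The SE of the arm difference is 0.12 × √(2/20) = 0.038, and the noncentrality is 0.13 / 0.038 = 3.43. The noncentral t with 38 df gives power of 91.6% (normal approximation 92.9%). The stated power of over 90% is confirmed.

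**Step 2: variance under ANCOVA.** Let rho be the correlation between baseline log10 titre and the time-weighted post-baseline mean. The documents do not give it, so it is an assumption. Assume also a common SD, s, for both.
- Change score variance: 2s²(1 − rho)
- ANCOVA residual variance: s²(1 − rho²)
- Ratio: (1 + rho)/2
- Estimating the slope at N = 40 inflates the variance by 1 + 1/(40 − 4) = 37/36, and one degree of freedom is lost (37 df).

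**Step 3: power with change SD 0.12 and difference 0.13.** The ratio is (1 + rho)/2 × 37/36.

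| rho | Variance ratio | CI narrower by | ANCOVA power |
|---|---|---|---|
| 0.3 | 0.668 | 18% | 98.3% |
| 0.5 | 0.771 | 12% | 96.7% |
| 0.7 | 0.874 | 6.5% | 94.6% |
| 0.9 | 0.976 | 1% | 92.2% |
| 0.95 | 1.002 | none | 91.5% |

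The unadjusted comparator is 91.6% throughout. Break-even in variance is where (1 + rho)/2 × 37/36 = 1, so rho = 72/37 − 1 = 0.946.

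**Step 4: if the SD is larger than planned (assumption), rho 0.5.**
- SD 0.16: 70.7% unadjusted, 81.3% with ANCOVA.
- SD 0.20: 51.7% unadjusted, 62.6% with ANCOVA.

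**Step 5: check by simulation.** With 20,000 trials per setting at rho 0.5 and SD 0.12, the SE of the arm difference was 0.0377 unadjusted and 0.0332 with ANCOVA. Type I error was close to 5% for both methods at each rho tried (0.3, 0.5, 0.7, 0.9).

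**The case against.** The strongest reply is that nothing here is wrong. A t-test on change from baseline is a valid randomised comparison, it analyses the quantity on which the trial was powered, and it delivers the stated power on the protocol's inputs. That stands: this is a matter of efficiency and pre-specification, not an error in the sample size.

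The gain also rests on an undocumented correlation. A reader might infer that precision is lost in every stratum of 40. The documents do not support that, because the gain shrinks to about 1% of CI width at rho 0.9 and disappears above about 0.946. Nor does a wide spread of baseline titres by itself strengthen the case. With equal SDs and a change SD of 0.12, the baseline SD is 0.12/√(2(1 − rho)), which is 0.12 at rho 0.5 and about 0.37 at break-even. Within that framework, a wider spread means a smaller gain.

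It is equally tempting to put a large figure on chance imbalance. Assuming a baseline SD of 0.3 and a slope of 0.5 gives an error SD of 0.5 × 0.3 × √(2/20) = 0.047 log10. That exceeds the whole SE of 0.038 implied by the protocol's SD, so it cannot hold on the plan's inputs.

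Finally, a reader might infer that the imbalance clause inflates the primary type I error. The text names the unadjusted t-test as the comparison and offers regression as something that may be done in addition, so the primary p value is identifiable. The covariates and the threshold for imbalance can reasonably be left to the analysis plan. What remains is that the protocol itself fixes the less efficient test and makes adjustment depend on the data.

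**Conclusion.** The point holds as a recommended improvement. The planned analysis is valid and meets its stated power, but it uses a baseline titre that every analysed participant has in a form that is usually less efficient.

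On the plan's SD of 0.12, always-fitted ANCOVA would move power from 91.6% to between 92.2% (rho 0.9) and 98.3% (rho 0.3). If the SD is really 0.16 or 0.20, the gain at rho 0.5 is about 11 percentage points. At very high correlation the cost is negligible: 91.5% against 91.6% at rho 0.95.

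These figures assume equal SDs at baseline and follow-up, a common slope in both arms, 20 analysed per arm, and a correlation that the documents do not supply. The direction is firm, but the size is not.

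**What to change.** - Make the primary analysis in each Group 1 sub-stratum, in Group 2 and for the anti-tetanus endpoint an ANCOVA that is always fitted: time-weighted AUC outcome on arm and the week 0 log10 titre of the same antibody. Using the AUC mean or its change from week 0 as the response gives the same arm effect.
- In the combined Group 1 analysis, add terms for stratum.
- Keep the unadjusted t-test as a supportive analysis.
- Delete the imbalance-triggered regression, or label any such analysis exploratory.
- State that the covariate is the titre at randomisation. The outcomes section counts 12 months from a booster, and in the deferred arms that booster is given at week 24. A week 24 pre-booster titre is post-randomisation and should not serve as the baseline covariate.

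The cost is wording in the protocol and in the statistical analysis plan, which is to be approved before data lock, and one degree of freedom per stratum. No new data or samples are needed, and the sample size can stay as it is.
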